## Abstract

**Background:**

Previous studies have explored the anti-diabetic effects of *Cinnamomum cassia* extract in vivo and in vitro. However, there are no studies at present exploring the effects of the indigenous species of Sri Lankan cinnamon (*Cinnamomum zeylanicum*) in patients with diabetes mellitus. The present study aims to evaluate the potential effects of *Cinnamomum zeylanicum* extract as a pharmaceutical agent in patients with type-2 diabetes mellitus.

**Methods/design:**

The study will be conducted as a randomized, double-blind, placebo-controlled clinical trial for a period of 4 months at the Medical Clinic, University Medical Unit, National Hospital of Sri Lanka. A total of 210 subjects with diabetes, in three equal groups, will be recruited for the study. The patients will be randomized in a 1:1:1 ratio according to the method of block randomization and the subjects will be randomly and equally assigned into two test groups (*n* = 70 each) and one placebo group (*n* = 70). The population will be stratified at randomization based on age, gender and disease severity. The treatment drug is a capsule containing *Cinnamomum zeylanicum* extract as the active ingredient and the placebo capsule will contain lactose monohydrate. Two doses of *Cinnamomum zeylanicum* extracts (250 mg and 500 mg of the cinnamon extract) will be used. The study drugs will be double blinded to both investigators and participants. The visits and the evaluations will be done as follows: screening (visit 0), 1 month (visit 1), 2 months (visit 2), 3 months (visit 3) and 4 months (visit 4). The following primary outcome measures will be evaluated: glycosylated hemoglobin (HbA_1_c), fasting plasma glucose (FPG) and serum insulin. Secondary outcome measures include: Body Mass Index (BMI) and other anthropometric parameters, blood pressure, total cholesterol, low-density lipoprotein cholesterol (LDL), high-density lipoprotein cholesterol (HDL) and triglycerides (TAG). Data will be analyzed using SPSS version 14.

**Discussion:**

We describe the protocol for a clinical trial design evaluating the effects of *Cinnamomum zeylanicum* (Ceylon cinnamon) in patients with type-2 diabetes mellitus. The result of the present study, positive or negative, should provide a step change in the evidence guiding current and future policies regarding the use of cinnamon dietary supplementation in patients with diabetes.

**Trial registration:**

Sri Lanka Clinical Trials Registry (SLCTR), identifier: SLCTR/2017/010 (http://slctr.lk/trials/714). Registered on 5 April 2017; study protocol version 3.1 21 March 2017.

**Electronic supplementary material:**

The online version of this article (doi:10.1186/s13063-017-2192-0) contains supplementary material, which is available to authorized users.

## Background

Diabetes mellitus is a leading cause of morbidity and mortality worldwide, with an estimated 80% of the world population with diabetes living in lower- and middle-income countries (LMICs) like Sri Lanka [1, 2]. Most patients with the disease have type-2 diabetes, characterized by insulin resistance and β-cell dysfunction, leading to ultimate pancreatic β-cell failure [3]. South Asians are known to have an increased predisposition for type-2 diabetes, due to genetic, biological and lifestyle factors [4, 5]. The causes of type-2 diabetes are multifactorial and includes both genetic and environmental factors [6]. Diet plays an important role on the incidence, severity and management of type-2 diabetes [7]. This has resulted in numerous studies focusing on dietary components that are beneficial either in the prevention and/or treatment of type-2 diabetes and the findings of these individual studies have been summarized in systematic reviews [8–10].

Cinnamon is one such dietary component that has been shown to contain biologically active substances that regulate blood glucose by insulin-mimetic properties, which enhances glucose uptake by activating insulin receptor kinase activity, auto-phosphorylation of the insulin receptor and glycogen synthase activity [11]. Cinnamon has two main varieties, *Cinnamomum cassia* (also known as *Cinnamomum aromaticum*) and *Cinnamomum zeylanicum*. Sri Lanka produces the largest quantity and best quality of cinnamon. *Cinnamomum zeylanicum*, also known as Ceylon cinnamon (the source of its Latin name, zeylanicum) or “true cinnamon” is indigenous to Sri Lanka [11]. One important difference between true cinnamon and cassia cinnamon is their coumarin content [12]. Coumarins posses strong anticoagulant properties and can have potentially toxic effects on the liver [13]. The coumarin content in Ceylon cinnamon is negligible and is not known to cause detrimental health effects, whereas the coumarin level in *Cinnamomum cassia* is much higher and can cause health risks if consumed in larger quantities on a regular basis [12]. Several countries have restricted the regular usage of *Cinnamomum cassia* as a result of this potential health hazard associated with high levels of coumarins [12].

However, it is important to note that previous studies have explored the anti-diabetic effects of *Cinnamomum cassia* extract in vivo and in vitro [14–18]. At present there are no studies exploring the effects of the indigenous species of Sri Lankan cinnamon (*Cinnamomum zeylanicum*) on diabetes mellitus in vivo in humans. Since, *Cinnamomum zeylanicum* has been shown to contain negligible amounts of coumarin, it may be possible that Ceylon cinnamon could be used in higher doses without toxic effects for longer durations [12, 19]. A phase-1 clinical trial conducted by our study team, where *Cinnamomum zeylanicum* was given as a regular daily supplementation to healthy adults for a period of 3 months, failed to reveal any significant adverse effects (unpublished data). The present paper describes the study protocol for a randomized, double-blind, placebo-controlled clinical trial evaluating the efficacy of *Cinnamomum zeylanicum* (Ceylon cinnamon) in patients with type-2 diabetes mellitus.

## Methods/design

This protocol was written following the Standard Protocol Items: Recommendations for Interventional Trials (SPIRIT) Checklist (see Additional file 1) [20]. The schedule of trial enrollment, interventions and assessments is presented in Fig. 1.

**Fig. 1 Fig1:**
[figure not shown]
Summarized study schedule at each visit in the clinical trial

### Objectives and hypothesis

Hypothesis: we hypothesize that the glycemic control of people with diabetes mellitus who are treated with *Cinnamomum zeylanicum* (Ceylon cinnamon) in addition to conventional treatment with oral hypoglycemic agents will be better than that of the control group treated only with oral hypoglycemic agents. We also hypothesize that other diabetes-related metabolic parameters (total cholesterol, triglycerides (TAG), high-density lipoprotein (HDL) cholesterol, low-density lipoprotein (LDL) cholesterol, and blood pressure) will be improved in the treatment group in comparison to the control group.

Objectives: the study evaluates the potential effects of *Cinnamomum zeylanicum* extract as a pharmaceutical agent in patients with type-2 diabetes in Sri Lanka. In addition to that the study evaluates the effects on serum lipids, anthropometric parameters, blood pressure and appetite and also studies the potential effects of regular administration of *Cinnamomum zeylanicum* extracts on liver and kidney function and the occurrence of self-reported side effects in patients with diabetes.

### Study design and setting

The study will be a phase-II/III, randomized, double-blind, placebo-controlled clinical trial. It will be conducted at the Medical Clinic, University Medical Unit, National Hospital of Sri Lanka for a period of 4 months, assessing the effects of the daily supplementation of capsules containing *Cinnamomum zeylanicum* in patients with type-2 diabetes mellitus. The Medical Clinic, University Medical Unit, National Hospital of Sri Lanka has around 400–500 patients with diabetes, attending the clinic on a monthly basis. The clinic operates 2 days per week and during all 4 weeks of a month. The duration of the trial will be 4 months, based on the evidence from previous research conducted by the investigators, and this duration is expected to be sufficient to identify changes in the primary glycemic outcomes (glycosylated hemoglobin (HbA1c), fasting plasma glucose (FPG) and serum insulin) assessed during the clinical trial [21].

### Sample size

The sample size was calculated using one-way analysis of variance (ANOVA), by the formula given below;$$ {n}_A=\left({\sigma^2}_A+{\sigma^2}_B/\kappa \right){\left(\frac{z_1{{{{}_{-}}_{\alpha}}_{/}}_{\tau }+{{z_1}_{-}}_{\beta }}{\mu_A-{\mu}_B}\right)}^2 $$

*n*
_*A*_ – sample size in one group
*σ*
_*A*_ – standard deviation of group A
*σ*
_*B*_ – standard deviation of group B
*κ* – sampling ratio
*α* – type-I error
*τ* – number of pairwise comparisons
*β* – type-II error
*μ*
_*A*_ – mean of group A
*μ*
_*B*_ – mean of group B

The number of patients required in a group for determination of a 0.75% reduction of HbA_1_c in a treatment group (*μ*
_*A*_
*–* 7.5%), in comparison with the placebo group (*μ*
_*B*_
*–* 6.75%) at 80% power (*β*), 95% confidence level (*α* – 0.05), for three pairwise comparisons (*τ*), with a sampling ratio of 1 (*κ*) is 62 in one group according to the above formula. The standard deviation of the HbA_1_c (*σ*
_*A*_ and *σ*
_*B*_) was taken as 1.4 based on evidence from previous research among Sri Lankan patients with diabetes [22]. Hence, the total sample required for the three groups will be 186. Therefore, a total of 210 subjects with diabetes in three equal groups will be recruited for the study, allowing for a dropout rate of 10%. Subjects will be randomly and equally assigned into two test groups (*n* = 70 each) and will receive either a *Cinnamomum zeylanicum* oral capsule (250 mg or 500 mg) or an identical placebo daily for 4 months.

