### Statistical analysis

Parametric (e.g., ANOVA) and non-parametric (e.g., Kruskal-Wallis test) statistical tests will be applied using the SPSS version 14 (SPSS Inc., Chicago, IL, USA) and Stata/SE 10.0 (Stata Corporation, College Station, TX, USA) for the data analysis. Data will be entered by a minimum number of dedicated staff and saved in a dedicated computer with password protection. For each of the outcomes, multilevel regression analysis will be used to examine differences between trial arms. For binary outcomes the model will be logistic and, for continuous outcomes, the model will be linear regression. All analyses will follow intention-to-treat principles and a prespecified analysis plan. Where appropriate, sensitivity analyses will be conducted (for example, control for additional covariates; and bootstrapped *p* values for skewed outcomes). In the case of missing data values, we will apply mean imputation and regression imputation where rates are low, and consider multiple imputations where they exceed 10%. Since multiple tests are performed simultaneously, a Bonferroni correction will be made during analysis to determine the critical *P* value for significance.

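### The 62 per arm rests on an undeclared one-sided Bonferroni quantile; with two-sided pairwise tests the stated 80% power is about 72%

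*Protocol article*

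**What the plan says.** In the protocol article, the Sample size section introduces the calculation with "The sample size was calculated using one-way analysis of variance (ANOVA), by the formula given below". The formula is a two-group comparison of means with the type-I quantile written as z(1−α/τ), where τ is the number of pairwise comparisons. The aim is "determination of a 0.75% reduction of HbA_1_c in a treatment group" of 0.75 percentage points, with a common SD of 1.4, α of 0.05 described as a 95% confidence level, 80% power, τ = 3 and equal allocation. The stated result "is 62 in one group according to the above formula". This becomes 186 in total, and 210 (70 per arm) to allow for 10% dropout.

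The treatment mean is given as 7.5%, and this is set "in comparison with the placebo group", whose mean is given as 6.75%.

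The Statistical analysis section states "Parametric (e.g., ANOVA) and non-parametric (e.g., Kruskal-Wallis test) statistical tests will be applied". It adds multilevel regression (linear for continuous outcomes) to examine differences between arms, and a Bonferroni correction. Neither section uses the term one-sided or two-sided.

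**The concern.** In a Bonferroni-adjusted two-sided comparison each test takes α/τ, split over two tails, so the quantile should be z(1−α/(2τ)). The printed formula leaves out the factor 2 and so puts the whole of α/τ in one tail. If the tests are then run two-sided, as the named methods imply, this formula gives too small a sample and overstates the power.

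What is at stake is how a null result is read. The Discussion says that either a positive or a negative result should shift the evidence guiding policy. A negative result read against a 20% chance of missing the target difference would really carry a chance of about 28%.

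The reversed means add to the confusion. Taken literally they describe a treatment that raises HbA1c, which a one-sided test for a reduction could not detect.

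**Working it through.** **Inputs, all from the Sample size section:** difference 0.75; SD 1.4 in both groups; κ = 1; α = 0.05; τ = 3, so α/τ = 0.01667; power 80%, so z(0.80) = 0.8416; 70 per arm randomised, or 70 × 0.9 = 63 after 10% dropout.

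**1. Reproduce the plan's figure.** With equal SDs and κ = 1 the formula becomes n = 2 × 1.4² × ((z + 0.8416)/0.75)².

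- Printed quantile: z(1 − 0.05/3) = 2.128.
- n = 3.92 × (2.970/0.75)² = 61.46, rounded up to 62. This matches the plan exactly.

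**2. Check whether another reading also gives 62.**

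| Comparisons (τ) | One-sided n | Two-sided n |
|---|---|---|
| 1 | 44 | 55 |
| 2 | 55 | 67 |
| 3 | **62** | **73** |

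Only the one-sided quantile with τ = 3 does.

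**3. Express this as a two-sided level.** One-sided 0.01667 is the same cut-off as two-sided 2 × 0.01667 = 0.0333 per comparison. Over three comparisons that is 3 × 0.0333 = 0.10, not the stated 0.05.

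**4. Two-sided requirement.** z(1 − 0.05/6) = 2.394.

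- n = 3.92 × (3.236/0.75)² = 72.96, rounded up to 73 evaluable per arm, or 219 in total.
- With 10% dropout: 73/0.9 = 81.1, so 82 per arm, or 246 in total, against 70 and 210 planned.

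**5. Power at the planned sizes.** Power = Φ(0.75/(1.4 × √(2/n)) − 2.394).

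| Per arm | Calculation | Power |
|---|---|---|
| 62 (the stated requirement) | Φ(2.983 − 2.394) | 72.2% |
| 63 (70 less 10%) | Φ(3.007 − 2.394) | 73.0% |
| 70 (no dropout) | Φ(3.169 − 2.394) | 78.1% |

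With the noncentral t distribution, power at 62 is 71.0% (two-group degrees of freedom) or 71.4% (three-group error degrees of freedom). For comparison, the one-sided test at 62 has 80.4% by the normal approximation.

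**6. Difference detectable with 80% power, two-sided, τ = 3.** (2.394 + 0.8416) × 1.4 × √(2/n) gives 0.81 at 62 or 63 per arm and 0.77 at 70.

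**7. The swapped means.** The difference enters the formula squared, so (7.5 − 6.75)² and (6.75 − 7.5)² are equal and n is unaffected.

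**The case against.** The best defence is that 62 is no miscalculation. It follows exactly from the printed formula, the document never writes two-sided, and the hypothesis is directional: control under cinnamon is expected to be better than under placebo. That much is true, and the fault is a mismatch between formula and tests, not a slip in the arithmetic. But a directional hypothesis does not declare a one-sided test; the stated level is "95% confidence level (*α* – 0.05"), without any mention of one tail, and the named tests have no direction. With two doses and placebo, one of the three pairwise comparisons is also 250 mg against 500 mg, for which the hypothesis gives no direction.

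A second objection is that 72% is not the power of every analysis in the plan. An omnibus ANOVA F test at 0.05, with the extreme means 0.75 apart, has 76–87% power at 62 per arm and 81–91% at 70, depending on where the middle mean is assumed to lie. This stands as a limit on the claim. It does not rescue the section, which sizes the trial on three Bonferroni-adjusted pairwise comparisons.

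Third, modest changes in the inputs would close the gap. At 63 per arm, 80% power needs an SD of 0.75/(3.236 × √(2/63)) = 1.30. Adjustment for baseline would bring 1.4 down to 1.30 if the correlation with baseline were about 0.37, since 1.4 × √(1 − 0.37²) = 1.30. That correlation is an assumption: the plan neither gives one nor counts on adjustment.

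Finally, the swapped means are a labelling slip in a sentence that plainly says reduction. That is accepted; they are a minor point.

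**Conclusion.** The concern holds. The 62 per arm depends on a one-sided quantile that the protocol does not declare and that does not match the tests it names. For one two-sided Bonferroni-adjusted pairwise comparison, power is about 72% at 62 per arm and 73% at the 63 expected after dropout, so the type-II error is 27–28% instead of 20%. Even 70 analysed per arm gives 78.1%, short of 80%.

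These figures assume SD 1.4, a true difference of 0.75, three comparisons, no covariate adjustment and two-sided testing. The last is inferred from the named methods and from the absence of any one-sided declaration. The type-I error of the eventual analysis is not affected; what is wrong is the stated power and the sample size attached to it. The reversed means contradict their own sentence but change no number.

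**What to change.** In the Sample size section:

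- Replace z(1−α/τ) by z(1−α/(2τ)) and say that testing is two-sided.
- Keep 210 patients, and restate power for the unadjusted three-comparison test as about 72% at 62 per arm (73% at 63). Alternatively, state that the difference detectable with 80% power is 0.81 points.
- Correct the labels so that placebo is 7.5% and treatment 6.75%.

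If 80% is to remain the claim, it needs its own justification: a baseline-adjusted model with a stated and sourced correlation, a smaller family of comparisons, or both. Restricting the family to each dose against placebo (τ = 2, two-sided) is not enough alone: the same formula requires 67 evaluable per arm, with power of 77.8% at 63 and 82.3% at 70.

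The cost is rewording one paragraph and reporting a less favourable power. No extra patients are needed, and the protocol says enrolment had not started.

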### Population

Diabetes is defined as the presence of a FPG ≥ 126 mg/dl or a plasma glucose level 2 h post oral glucose load of ≥ 200 mg/dl, or both. Participants will be recruited on a voluntary basis from a cohort of patients with diabetes mellitus attending the Medical Clinic, University Medical Unit, National Hospital of Sri Lanka. Informed written consent will be obtained from all study participants. Details of the inclusion and exclusion criteria are given below.

### Inclusion and exclusion criteria

#### Inclusion criteria

Age 18–70 yearsDiagnosed type-2 diabetes mellitus during the last 5 yearsCurrently only taking metformin or a sulphonylurea, or both (less than or equal to two oral hypoglycemic agents) for the last 3 monthsHbA_1_c 6.5–8.0% and or FBS 126–200 mg/dl

#### Exclusion criteria

Patients with an allergy to cinnamonAlcohol consumption > 20 g/dayPatients with diagnosed alcoholic liver disease (ALD), cirrhosis or abnormal baseline liver function testsPatients using insulin therapyPatients with raised baseline serum creatinine level (>1.5 mg/dl in men or > 1.2 mg/dl in women)Lactation, pregnancy or unwillingness to use an effective form of birth control for women of childbearing yearsPatients with symptoms suggestive of peptic ulcer disease and those with a past history of peptic ulcerationPatients with any malignancyPatients with unrelated chronic illnessPatients with cardiac, liver or respiratory failurePatients with bleeding disorders and who are taking coumarin derivatives (e.g., warfarin)Any condition that, in the opinion of the primary investigator, would contraindicate the patient’s participation

#### Suspension criteria

Subject’s demand to discontinue the studySerious adverse events or unusual changes in clinical test resultsPrincipal investigator’s decision to terminate the study (low rates of compliance, complications or inability to tolerate the study for various reasons)

### Randomization

Randomization for the parallel treatment arms will be carried out by the principal investigator after checking the inclusion and exclusion criteria. The patients will be randomized in a 1:1:1 ratio according to the method of block randomization with a block size of 15. The population will be stratified at randomization based on, age (below 50 years and 50 years and over), gender and the severity of the disease (HbA_1_c 6.5–7.5% and 7.5–8.0%) to ensure equal distribution of these variables in the three arms. The randomization sequence would be generated using the SPSS statistical software package (version 14.0).

### Blinding

The investigators and patients are blind to the treatment allocations. The medication will be delivered in similar packets and labels, each with its own sequence number. The allocation sequence number will be generated by one of the investigators not involved in managing patients. Envelopes containing a monthly supply of either placebo or cinnamon will be prepared according to the randomization sequence and supplied to the patients by the principal investigator or research assistants when they are randomized to the trial.

### Interventions

The treatment drug is a capsule containing *Cinnamomum zeylanicum* extract as the active ingredient; it will have a white-colored body and a capsules. Two doses of cinnamon will be used in the present study (250 mg and 500 mg) based on data arising from previous research [17, 21]. Stem bark of *Cinnamomum zeylanicum* will be extracted to distilled water using Soxlet apparatus and the resulting hot-water extract will be freeze-dried to obtain a crude water extract from which the capsules will be prepared. The placebo capsule will contain lactose monohydrate and stearic acid. The weight of each cinnamon oral capsule will be 300 mg (cinnamon + inert filler material). The placebo oral capsule will be identical in shape, size, weight and texture to the *Cinnamomum zeylanicum* oral capsule. In order to mask the aroma, cinnamon quills would be put into packets containing both the placebo and cinnamon capsules. Each group would be given two oral capsules before breakfast for daily usage for a period of 4 months (Table 1). Capsules will initially be given at visit 0 for a period of 1 month, and subsequently a monthly supply will be given to participants at each clinic visit.

**Table 1 Tab1:** Study groups in the clinical trial

Group	Number of capsules (1 = 250 mg of cinnamon)		
	Cinnamon	Placebo	Total
Group 1 (250 mg of cinnamon)	1	1	2
Group 2 (500 mg of cinnamon)	2	0	2
Group 3 (placebo)	0	2	2

### Study groups

#### Treatment groups

To evaluate a dose-response relationship, the phase-II study will include two treatment groups. The groups will receive *Cinnamomum zeylanicum* doses of either 250 mg or 500 mg based on results arising from previous research:Group 1 – *Cinnamomum zeylanicum* dose 250 mg dailyGroup 2 – *Cinnamomum zeylanicum* dose 500 mg daily

#### Control group

3.Group 3 – placebo group

### Study period

The study will be for a period of 4 months and the visits and the evaluations will be done as follows: screening (visit 0), 1 month (visit 1), 2 months (visit 2), 3 months (visit 3) and 4 months (visit 4) (Fig. 1).

### Outcomes

#### Primary outcome index

Primary glycemic outcomes assessed would be the HbA_1_c, FPG and serum insulin.

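### Three unranked primary outcomes and a Bonferroni correction rest on a sample size that divides α only over three HbA1c arm pairs: either HbA1c power is 58–67% instead of 80%, or the error over the primary outcomes is about 10–13%

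*Protocol article*

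**What the plan says.** Primary outcome index: "Primary glycemic outcomes assessed would be the HbA_1_c, FPG and serum insulin". The Abstract and the Study design and setting section give the same three. No section puts one first, sets a testing order, or requires success on all three.

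Sample size: "The sample size was calculated using one-way analysis of variance (ANOVA), by the formula given below". The target is "determination of a 0.75% reduction of HbA_1_c in a treatment group". The printed critical value is z(1−α/τ), where τ is the "number of pairwise comparisons". The result is given as "95% confidence level (*α* – 0.05), for three pairwise comparisons (*τ*), with a sampling ratio of 1 (*κ*) is 62 in one group". No effect size or standard deviation is given there for fasting glucose or insulin.

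Statistical analysis: "Since multiple tests are performed simultaneously, a Bonferroni correction will be made during analysis". The number of tests and the family are not given.

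Treatment groups: "To evaluate a dose-response relationship, the phase-II study will include two treatment groups". This gives the comparison of the two doses a stated purpose.

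**The concern.** The sample size counts arm pairs but not outcomes, while the analysis section makes its correction depend on how many tests are run. With three equal primary outcomes the two do not match.

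If the correction covers all primary tests, each HbA1c comparison is judged at a stricter threshold than the one used to size the trial, and the stated 80% is not delivered. If it stays with the arm pairs, as the sample size assumes, nothing protects the choice among three outcomes, and success on any one of them can be claimed at well above 5%. At stake is what a positive result would mean, and whether a negative HbA1c result would be informative.

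**Working it through.** **Inputs (Sample size section).** HbA1c difference 0.75; SD 1.4 in each group; α = 0.05; power 80%; τ = 3; equal groups; 62 per group, 186 in total; 210 recruited (70 per group) for 10% dropout. From the Primary outcome index: three outcomes.

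**1. Reproduce the 62.** The printed formula is n = 2σ²[(z(1−α/τ) + z(1−β))/δ]². With z(1−0.05/3) = 2.128 and z(0.80) = 0.842:

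n = 2 × 1.96 × (2.970/0.75)² ≈ 61.5, so 62. Reproduced.

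The printed critical value is one-sided. The two-sided value z(1−0.05/6) = 2.394 gives 73 per group, not 62. The document does not state sidedness in words, so both bases are carried below.

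**2. Power for one HbA1c pair under wider families.** Power = Φ(δ/SE − z), with SE = 1.4 × √(2/n).

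- n = 62: SE = 0.2514, δ/SE = 2.983
- n = 70: SE = 0.2366, δ/SE = 3.169

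| Bonferroni family | One-sided z | Power at 62 | Power at 70 | Two-sided z | Power at 62 | Power at 70 |
|---|---|---|---|---|---|---|
| 3 tests (HbA1c, three pairs) | 2.128 | 80.4% | 85.1% | 2.394 | 72.2% | 78.1% |
| 6 tests (three outcomes, two placebo pairs) | 2.394 | 72.2% | 78.1% | 2.638 | 63.5% | 70.2% |
| 9 tests (three outcomes, three pairs) | 2.539 | 67.1% | 73.6% | 2.773 | 58.3% | 65.4% |

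The 70-per-arm columns assume no dropout. At 10% dropout (63 per arm), the nine-test figures are 68.0% one-sided and 59.2% two-sided.

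**3. Separate the two causes.** Going from three to nine tests costs 80.4 − 67.1 = 13.3 points one-sided, or 72.2 − 58.3 = 13.9 points two-sided. The change from one-sided to two-sided at three tests costs 80.4 − 72.2 = 8.2 points and has nothing to do with the number of outcomes.

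**4. Size needed for 80% at α/9.** One-sided, 80 per group: 240 in total, 267 recruited at 10% dropout. Two-sided, 92 per group (91.05 rounded up): 276 in total, 307 recruited.

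**5. Error if only the arm pairs are corrected.** If each outcome used exactly 5% and the outcomes were independent, the error would be 1 − 0.95³ = 14.3%. Treating all nine tests as independent gives 1 − (1 − 0.05/3)⁹ = 14.0%. But the three pairs share groups, so Bonferroni over them is slightly conservative: in simulation one outcome uses about 4.4%. Simulating all nine two-sided tests at 0.05/3 under no effect, with a common correlation between outcomes (assumed, since the document gives none):

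| Correlation | 0 | 0.3 | 0.5 | 0.7 |
|---|---|---|---|---|
| Error over the three outcomes | 12.6% | 12.1% | 11.3% | 9.9% |

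One-sided tests give nearly the same range, 12.8% down to 9.7%.

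**6. One primary outcome, HbA1c.** Three pairs: 80.4% one-sided, 72.2% two-sided. Two placebo comparisons only: one-sided z = 1.960 gives 84.7%; two-sided z = 2.241 gives 77.1%. All at 62 per arm, without covariate adjustment.

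**The case against.** The strongest reply is that the exact Bonferroni family is ordinary analysis-plan content. The protocol refers to such a plan, which is not shown. That stands: the missing definition is not itself a fault. But the outcomes, the sample size and the method of correction are fixed here. Under Bonferroni, counting the outcomes leaves HbA1c short of 80%, and not counting them leaves the primary set unprotected. Only narrowing the set or adding a testing order avoids both.

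A second reply is that the analysis section does not confine the correction to arm pairs, so the error problem may never arise. That is fair. In that case the power problem applies.

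Four stronger readings are tempting, and the documents do not support them:

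- **That multiplicity alone takes power from 80% to 58%.** The 80% belongs to a one-sided formula and the 58% to two-sided tests. About 8 of the 22 points come from sidedness.
- **That the error is 14%.** That is close to the ceiling. It needs independent outcomes and the full 5% spent on each.
- **That every secondary outcome joins the corrected family.** No section defines such a family.
- **That the comparison of 250 mg with 500 mg is surplus or hopeless.** The Treatment groups section states a dose-response aim and the sample size counts this pair. Whether it could show 0.75 depends on how well the lower dose works, which the documents do not say.

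**Conclusion.** The mismatch is real. With α spread over the nine primary tests, HbA1c power at 62 per arm is 67% on the protocol's one-sided basis, or 58% two-sided. Full retention of 70 per arm raises this only to 74% or 65%. With α spread over arm pairs only, the error across the three primary outcomes is about 10–13%, roughly twice 5%, with 14% as a near-ceiling. These are alternatives: the plan faces one or the other, not both.

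The power figures use the protocol's own difference and SD, a normal approximation and no covariate adjustment. The error range rests on assumed correlations of 0.7 down to 0.

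**What to change.** Before enrolment (the Trial status section says it had not started):

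1. Name HbA1c at 4 months as the single primary outcome, since it is the only one sized. Move fasting glucose and serum insulin to secondary.
2. State that the primary Bonferroni or Holm family is the HbA1c arm comparisons, and whether that means all three pairs or only the two placebo comparisons.
3. State sidedness and restate the power to match. Two-sided at 62 per arm, unadjusted, it is 72% for three pairs or 77% for two placebo comparisons.

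If all three outcomes stay primary, define the family and restate HbA1c power as 58–67% at 62 per arm, or re-size to 80 (one-sided) or 92 (two-sided) evaluable per arm.

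The main fix changes wording in the protocol and registry entry and needs no more patients. Its price is that fasting glucose and insulin can no longer be claimed as primary, and with two-sided tests the stated power is less favourable than 80%.
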